### **1.2 Secondary objectives**

Secondary objectives include the following.

- Incidence of malnutrition

Determine the efficacy of 14 days MNP supplementation versus a control group and RUTF versus MNP on the incidence of acute malnutrition during 6 months follow-up,

- Frequency of morbidity

Determine the effect of 14 days supplementation on the frequency of morbidity (3 study diseases) during 6 months follow-up, comparing both intervention groups to the control group and comparing RUTF to MNP)

- Weight changes immediately after intervention period, measured at day-14 and day-28

Measure mean weight change (total change and rate (grams/kg/day) of change), comparing both intervention groups separately (RUTF and MNP) to the control group

Determine frequency of 'no weight gain and/or weight loss', comparing both intervention groups separately (RUTF and MNP) to the control group

Assess if provision of 14 days of RUTF or MNP supplement promotes a sustained weight gain, measured after 28-days of follow-up, comparing both intervention groups separately (RUTF and MNP) to the control group

- Evaluation of several subgroup to assess potential effect modifiers.

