### 5.4 Secondary analysis of the primary endpoint

#### 5.4.1 Treatment group comparisons

Although the study is primarily powered for the comparison between the RUTF and control group the other groups will be compared as well, keeping in mind that the sample size might not be large enough to obtain significant results.

Since there are three interventional groups to be compared, a hierarchical test procedure will be used to account for multiplicity.

i) In a first (primary) step, RUTF will be compared to the control group which is described above as analysis of primary outcome

If the RUTF group is not significantly different at a 0.05 level (two-sided test), the hierarchical procedure is stopped (all following analyses will be considered explorative). If the RUTF group is significantly different at a 0.05 level, the hierarchical procedure is continued with step 2.

ii) In the second step, MNP will be compared to the control group

The hypotheses in this step are

$$H_0: \text{rate}_{\text{MNP}} = \text{rate}_{\text{Control}}$$

vs.

$$H_1: \text{rate}_{\text{MNP}} \neq \text{rate}_{\text{Control}}$$

where  $\text{rate}_{\text{MNP}}$  = rate of “negative nutritional outcome” in the children in the MNP group, and  $\text{rate}_{\text{Control}}$  = rate of “negative nutritional outcome” in the children in the control group.

If the treatment factor is not significant at a 0.05 level (two-sided test), the hierarchical procedure is stopped (all following analyses will be considered explorative). If the treatment factor is significant at a 0.05 level, the hierarchical procedure is continued with step iii).

iii) In the third step, RUTF will be compared to MNP (non-inferiority test).

The hypotheses in this step are

$$H_0: \text{rate}_{\text{RUTF}} - \text{rate}_{\text{MNP}} > -\delta$$

vs.

$$H_1: \text{rate}_{\text{RUTF}} - \text{rate}_{\text{MNP}} \leq -\delta$$

where  $\text{rate}_{\text{RUTF}}$ =rate of “negative nutritional outcome” in the children in the RUTF group,  $\text{rate}_{\text{MNP}}$ =rate of “negative nutritional outcome” in the children in the MNP group, and  $\delta$ =inferiority margin.

As non-inferiority margin, a  $\delta$  of 2% (absolute value) will be used (i.e. allowing a slightly worse result in the MNP compared to the RUTF group). The third step will be tested at a 0.025 level (one-sided test), by a one-sided 97.5% confidence interval of the difference in rates between the RUTF and the MNP group.

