The general problem of assay sensitivity in non-inferiority comparisons can be addressed in this study by the 3-arm design including a control group receiving no nutritional supplementation. Thus, superiority of the two nutritional interventions (RUTF and MNP) versus no intervention can be evaluated prior to the non-inferiority comparison.

These step-wise comparisons of rates among treatment groups will be performed by the same Poisson regression model, adjusted for nutritional status at enrolment (fixed effect) as described above, i.e. performed within one model including the three intervention groups with contrasts for each two-group comparison. The results will be presented as rates for each intervention group, and rate ratios for the pair-wise comparison (each with 95% confidence intervals).

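### A confirmatory RUTF-versus-MNP result is possible only after MNP differs from control; a difference test straight after step i would cost no alpha, and the printed step iii hypotheses need correcting

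*SAP*

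**What the plan says.** Section 1.2 of the SAP lists among its secondary objectives: "Determine the efficacy of 14 days MNP supplementation versus a control group and RUTF versus MNP on the incidence of acute malnutrition". It gives no direction for RUTF versus MNP and does not call the comparison confirmatory.

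Section 5.4.1 says that "a hierarchical test procedure will be used to account for multiplicity". The steps are:

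- **Step i**, RUTF versus control: "If the RUTF group is not significantly different at a 0.05 level (two-sided test), the hierarchical procedure is stopped".
- **Step ii**, MNP versus control: "If the treatment factor is not significant at a 0.05 level (two-sided test), the hierarchical procedure is stopped", and later analyses become explorative.
- **Step iii**, RUTF versus MNP: "In the third step, RUTF will be compared to MNP (non-inferiority test"), with a margin δ of 2% (absolute), at one-sided 0.025. The prose explains the margin as room for MNP to do slightly worse than RUTF. The printed alternative is rate(RUTF) − rate(MNP) ≤ −δ.

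The reason given for the order is assay sensitivity: "superiority of the two nutritional interventions (RUTF and MNP) versus no intervention can be evaluated prior to the non-inferiority comparison". Sections 5.3 and 5.4.1 also provide one three-arm Poisson model with pairwise contrasts, and rate ratios with 95% confidence intervals.

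**The concern.** The RUTF-MNP contrast is a named objective and has a place in the formal hierarchy, but its only route to a confirmatory result runs through MNP versus control. If RUTF works and MNP does not, the procedure ends at step ii. That is the situation in which a reader would most want to know whether RUTF is better than MNP, and the answer is then explorative even with a very small p-value.

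The assay-sensitivity argument explains why a non-inferiority claim for MNP should wait until MNP has been shown to work. It gives no reason for a test of difference between RUTF and MNP to wait.

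Two further weaknesses sit in the same steps. The step ii gate is a two-sided difference, so a result with MNP significantly worse than control would also open step iii. And the printed step iii alternative runs opposite to its label and to the explanation of the margin.

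**Working it through.** **Inputs from the SAP.** Steps i and ii are two-sided at 0.05; step iii is one-sided at 0.025. Both use the critical value 1.960, so the levels agree. The SAP gives no sample size, event rate or power, so there is no design figure to reproduce. Everything numerical below rests on assumed inputs.

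**Why a difference test after step i is free.** There are three equality nulls: RUTF = control, MNP = control, RUTF = MNP.

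- If RUTF = control is true, any false rejection needs step i to reject wrongly, which has probability at most 0.05.
- If RUTF = control is false, MNP = control and RUTF = MNP cannot both be true, since together they would imply RUTF = control. At most one true equality null remains, tested at 0.05.
- The non-inferiority null (MNP worse than RUTF by δ or more) cannot hold together with RUTF = MNP. If it holds together with MNP = control, it can be rejected only after that null has been wrongly rejected, so it adds nothing. If it is the only true null, its error is at most 0.025.

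**Size of the loss.** Event counts per arm were simulated as Poisson, with Wald tests z = ln(rate ratio) / √(1/e₁ + 1/e₂), where e₁ and e₂ are the two event counts. In the main case (700 per arm, control rate 0.25 first events per child over 6 months, RUTF ratio 0.7, MNP = control) the expected events are:

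- control and MNP: 700 × 0.25 = 175 each
- RUTF: 175 × 0.7 = 122.5

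For RUTF versus control, z ≈ ln(0.7) / √(1/175 + 1/122.5) = −0.357 / 0.118 ≈ −3.03, and simulated power for step i is about 86%.

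'As written' counts trials with steps i and ii significant and RUTF significantly better than MNP. This is generous, because it lets step iii be read as an ordinary superiority test. 'With the fix' requires step i and RUTF better than MNP.

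| Assumed case | As written | With the fix |
|---|---|---|
| 700 per arm, rate 0.25, RUTF 0.7, MNP = control | 2.2% | 77% |
| 400 per arm, rate 0.15, RUTF 0.7, MNP = control | 0.3% | 26% |
| 1000 per arm, rate 0.25, RUTF 0.6, MNP = control | 4.9% | 99.8% |
| 700 per arm, rate 0.25, RUTF 0.7, MNP 0.85 | 4.6% | 34% |

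In the first case, RUTF beats both control and MNP while the gate is closed in about 75% of trials. Of the 2.2%, about 1.1 points are trials in which MNP is significantly worse than control.

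**Cross-check without rates.** A normal approximation with equal arms and MNP = control, fixing only the power of step i, gives:

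| Power of step i | Step iii reached | RUTF better than MNP, with the fix |
|---|---|---|
| 80% | 3.4% | 69% |
| 90% | 3.9% | 83% |

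**Family-wise error of the amended procedure (Poisson simulation).**

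| Configuration | Error |
|---|---|
| All equal | 0.050 |
| Only RUTF effective, 700 per arm | 0.036 |
| Only RUTF effective, 2000 per arm | 0.049 to 0.050 |
| MNP = RUTF, 700 per arm | 0.036 |
| MNP = RUTF, 2000 per arm | 0.049 to 0.050 |
| Only MNP effective | 0.050 |
| MNP exactly at the margin | 0.025 |

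**Direction of step iii.** The outcome is harmful, so rate(RUTF) − rate(MNP) ≤ −δ means that the RUTF rate is lower by at least δ, that is, RUTF is better by the margin or more. Non-inferiority of MNP is the complement: rate(RUTF) − rate(MNP) > −δ. The printed null and alternative are exchanged relative to the label and the prose.

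**The case against.** The strongest reply is that nothing promised has been broken. The objective is secondary, and the SAP says that the study is primarily powered for RUTF versus control and that the other comparisons may be too small. It states what follows a failed step: "the hierarchical procedure is stopped (all following analyses will be considered explorative"). A fixed sequence is valid, and the order has a stated reason. The RUTF-MNP rate ratio and its confidence interval are planned from the three-arm model whatever the gate does, so what is lost is confirmatory status, not the estimate. All of this stands, and it sets the weight of the point. It does not explain why an inference that costs no alpha should be given up on a contrast the SAP itself placed in its hierarchy.

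A second reply concerns size: the percentages depend on assumed inputs. That is also fair. The smallest case has only about 43% power for step i, which fits poorly with a trial powered for that comparison. The logic of the gate does not depend on these inputs.

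A reader might go further and infer that the plan never tests whether RUTF is better than MNP. The SAP does not support that: read literally, the printed step iii alternative is a superiority statement for RUTF, by a margin. It contradicts its own label and explanation, so it cannot serve as an intended superiority test, and it lies behind the same gate. Nor is it right that the gate is MNP beating control; as written it is a difference in either direction.

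**Conclusion.** The point holds as a worthwhile improvement in power plus a correction of the step iii wording. It is not a type I error fault. A reader might take it as a broken objective, but the SAP nowhere promises a confirmatory answer on RUTF versus MNP and it discloses the explorative fallback.

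If RUTF works and MNP does not, the chance of a confirmatory RUTF-better-than-MNP result is about 2% as written against about 77% with the amendment in the main assumed case. Over the assumed cases with MNP = control, it runs from 0.3% against 26% to 4.9% against 99.8%. If MNP has a partial effect, the gain is smaller (4.6% against 34%). These figures rest on assumed arm sizes, rates and effects. The error-rate argument does not, apart from treating each single test as holding its nominal level.

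The reversed step iii hypotheses and the undirected gate are defects on the face of the text and need correcting whether or not the difference test is added.

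**What to change.** Amend section 5.4.1 as follows:

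1. If step i is significant in favour of RUTF, test two contrasts, each two-sided at 0.05 and neither conditional on the other: (ii-a) MNP versus control, and (ii-b) RUTF versus MNP for a difference.
2. Keep the non-inferiority test (iii), conditional on ii-a being significant in favour of MNP.
3. Restate the step iii hypotheses to match the stated aim that MNP is not worse than RUTF by more than δ: H0: rate(RUTF) − rate(MNP) ≤ −δ; H1: rate(RUTF) − rate(MNP) > −δ.
4. Add one sentence saying that family-wise error stays at 0.05 because, once RUTF differs from control, at most one of the ii-a and ii-b nulls can be true.

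The cost is a few sentences. The RUTF-MNP contrast already comes from the planned three-arm model, so no patients, alpha or extra modelling are needed. Like any change to a test hierarchy, it should be made before treatment allocation is unblinded.

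### SAP 5.4.1, step iii: the null and alternative of the non-inferiority test are exchanged, so the printed test can only show that MNP is inferior

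*SAP*

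**What the plan says.** SAP section 5.4.1 sets out three ordered comparisons: RUTF against control, MNP against control, and then RUTF against MNP. The last is introduced as follows: "In the third step, RUTF will be compared to MNP (non-inferiority test".

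The hypotheses printed for it are:

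- Null: "H_0: \text{rate}_{\text{RUTF}} - \text{rate}_{\text{MNP}} > -\delta"
- Alternative: "H_1: \text{rate}_{\text{RUTF}} - \text{rate}_{\text{MNP}} \leq -\delta"

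On the margin, the SAP says that "a $\delta$ of 2% (absolute value) will be used", and it explains the purpose as "allowing a slightly worse result in the MNP compared to the RUTF group". On the decision, it says: "The third step will be tested at a 0.025 level (one-sided test), by a one-sided 97.5% confidence interval of the difference in rates" between RUTF and MNP. It does not say which confidence limit is used or what value it is compared with.

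Sections 3.1 and 5.3 define the rate as first negative nutritional outcomes divided by observed person-time, so a higher rate is worse.

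**The concern.** In a non-inferiority test, the claim to be proved belongs in the alternative. Here that claim is that MNP is worse than RUTF by less than the margin. The SAP places it in the null and makes the opposite statement the alternative. The formulae and the explanatory prose of the same step therefore point in opposite directions.

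The last formal conclusion of the hierarchy is at stake. An analyst who follows the formulae would count a rejection as success, although it is evidence that MNP breaches the margin. An analyst who follows the prose would test the intended claim. A pre-specified plan should not leave both routes open.

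**Working it through.** **Inputs from the SAP.** Adverse endpoint (3.1); rate = first events / person-time (5.3); δ = 2% absolute, with MNP the arm allowed to be worse (5.4.1); one-sided α = 0.025 with a one-sided 97.5% interval (5.4.1). The two are consistent: z = 1.960.

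**Step 1, signs.** Let D = RUTF rate − MNP rate. If MNP is worse, its rate is higher and D is negative.

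- MNP worse by less than δ: MNP rate < RUTF rate + δ, so D > −δ. This is non-inferiority of MNP.
- MNP worse by at least δ: MNP rate ≥ RUTF rate + δ, so D ≤ −δ. This is inferiority.

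**Step 2, comparison with the print.**

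| | Printed in the SAP | Needed for the stated purpose |
|---|---|---|
| Null | D > −δ (non-inferior) | D ≤ −δ (inferior) |
| Alternative | D ≤ −δ (inferior) | D > −δ (non-inferior) |

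Rejecting the printed null supports inferiority. Failing to reject it proves nothing. So neither outcome establishes non-inferiority.

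**Step 3, does another reading rescue it?** Suppose RUTF were the arm under test. Its non-inferiority would need the alternative D < +δ. The printed alternative, D ≤ −δ, would then say that RUTF is better by at least the margin, which is superiority by a margin. That reading also contradicts the sentence on which arm may be slightly worse.

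**Step 4, does other text correct it?** No. The confidence-interval sentence names neither the limit nor the comparison value. The rest of 5.4.1 gives the model and the presentation of results but no decision rule for step iii.

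**Step 5, illustration.** The SAP gives no sample size or event rate, so there is no figure of its own to reproduce. Assumptions: the margin is read as 0.02 per child per 6 months (the SAP gives no person-time unit), the RUTF rate is 0.10 to 0.30, there are 300 to 5000 children per arm, and a normal approximation holds with

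SE = √(RUTF rate/n + MNP rate/n).

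- Printed test: reject if the upper limit of D ≤ −0.02. Probability = Φ[(−0.02 − D)/SE − 1.960].
- Exchanged test: declare non-inferiority if the lower limit of D > −0.02. Probability = 1 − Φ[(−0.02 − D)/SE + 1.960].

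Example with RUTF rate 0.20 and n = 1500:

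- Equal arms: SE = √(0.40/1500) = 0.01633, and −0.02/SE = −1.225. Printed: Φ(−3.185) = 0.0007. Exchanged: 1 − Φ(0.735) = 0.231.
- MNP worse by 0.06: SE = √(0.46/1500) = 0.01751, and 0.04/SE = 2.284. Printed: Φ(0.324) = 0.627.

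Results at a RUTF rate of 0.20 (printed test rejects / exchanged test declares non-inferiority):

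| MNP worse by | n = 300 | n = 700 | n = 1500 | n = 5000 |
|---|---|---|---|---|
| 0 | 0.0061 / 0.079 | 0.0026 / 0.131 | 0.0007 / 0.231 | 0.00001 / 0.609 |
| 0.02 | 0.025 / 0.025 | 0.025 / 0.025 | 0.025 / 0.025 | 0.025 / 0.025 |
| 0.04 | 0.075 / 0.0065 | 0.123 / 0.0029 | 0.214 / 0.0009 | 0.568 / <0.0001 |
| 0.06 | 0.174 / 0.0014 | 0.345 / 0.0002 | 0.627 / <0.0001 | 0.986 / <0.0001 |

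Over the whole assumed range, an equally good MNP rejects the printed null with probability at most 0.0080 (rate 0.30, n = 300). A larger sample makes that rejection rarer, which is the reverse of how a non-inferiority test behaves.

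**The case against.** The strongest reply is that the intent is plain. The step is labelled a non-inferiority test, the prose says which arm may be slightly worse, and the decision rests on a confidence interval. A careful statistician could compare the lower limit with −2% and reach the intended conclusion. This stands as a limit on the consequence: a reader might infer that the reported conclusion is bound to be wrong, and the SAP does not support that. It does not remove the fault, because the interval sentence states no rule and the formulae are the only formal statement of the test.

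It is also fair to say that step iii is reached only after two significant results, and that the SAP itself warns that comparisons other than RUTF versus control may lack sample size.

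A reader might further infer that the route into step iii is faulty, because step ii says: "If the treatment factor is significant at a 0.05 level, the hierarchical procedure is continued with step iii". In a three-group model, the treatment factor could mean a global test on two degrees of freedom, which RUTF alone could make significant. The document does not support that reading. Step ii prints equality of the MNP and control rates as its null, and sections 5.3 and 5.4.1 specify a contrast for each pair of groups within the single model. The deciding test is thus the MNP-versus-control contrast, and the phrase is only loose.

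Nor is the two-sided form of steps i and ii an error. The direction shows in the reported rate ratio, and 5.4.1 says that "superiority of the two nutritional interventions (RUTF and MNP) versus no intervention can be evaluated prior to the non-inferiority comparison". Naming the direction would be a clarification.

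**Conclusion.** The point holds. The hypotheses of step iii are reversed for the stated purpose, and nothing else in the SAP corrects them. This rests on the signs and the direction of the endpoint alone. The probabilities above are illustrations that depend on the assumed rates, arm sizes and unit of the margin.

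The effect is confined to the third step of the hierarchy and to the analyses that repeat it, such as the per-protocol analysis in 5.4.5. The RUTF-versus-control and MNP-versus-control comparisons keep their validity. Because this is a formal decision rule that tests the opposite of its purpose, and the repair is trivial, it should be corrected before the analysis is run.

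**What to change.** In section 5.4.1, step iii:

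- State the null as RUTF rate − MNP rate ≤ −δ and the alternative as RUTF rate − MNP rate > −δ. The exchange also puts the boundary value in the null, where it belongs.
- Add the decision rule: MNP is declared non-inferior to RUTF if the lower one-sided 97.5% confidence limit of RUTF rate − MNP rate lies above −δ.

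As a minor clarification in step ii, replace the reference to the treatment factor with the MNP-versus-control contrast in favour of MNP, in line with the contrasts already specified in that section.

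The cost is SAP wording only. The design, data collection, model and significance levels do not change.

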#### 5.4.2 Further adjustments

In case of relevant differences in baseline characteristics additional adjustment(s) for these factors will be performed within the model described in 5.4.1 to address potential confounding.

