### **3 Endpoints**

#### **3.1 Primary endpoint**

The primary endpoint is “negative nutritional outcome (NNO)” of a child within the 6 months follow-up period. The incidence of a negative nutritional outcome will be defined in two different ways according to the baseline nutritional status:

- for children with no malnourishment at time of entry into study, “negative nutritional outcome” is defined as progression to moderate or severe malnourishment,
- for children with moderate malnourishment at time of entry into study, “negative nutritional outcome” is defined as loss of  $\geq 10\%$  of baseline weight or progression to severe malnourishment, whichever is reached first.

Thus, the event of a child reaching a “negative nutritional outcome” at least once within 6 months of follow-up period will be compared between the three study groups.

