# **5 Statistical analysis**

## **5.1 Analysis of baseline data**

All available data at baseline will be analysed descriptively for each intervention group and in total. Results will be summarised as frequencies and percentages for nominal data; as means, standard deviations, and range for continuous data; and as medians, quartiles, and ranges for ordinal data.

Differences regarding baseline variables will be checked for clinical relevance between the three treatment groups.

The flow of participants will be described (e.g. number screened, recruited, randomized, emergency unblinding, etc.). Number and reasons for drop-out, lost-to-follow-up, or withdrawal will be presented. If possible respondents and non-respondent will be compared.

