### 5.3 Primary analysis of primary endpoint

The primary endpoint is “negative nutritional outcome” of a child within the 6 months follow-up period. The incidence rate (in formulae below referred to simply as ‘rate’) of “negative nutritional outcome” will be computed as the number of events divided by total observed person-time in each treatment group. As an “event” the first time a child reaches a negative nutritional outcome will be used. The primary analysis of the primary endpoint will be performed on the intention to treat population with no imputation of missing data.

In the primary analysis, RUTF will be compared to the control group

The hypotheses in this step are

$$H_0: \text{rate}_{\text{RUTF}} = \text{rate}_{\text{Control}}$$

vs.

$$H_1: \text{rate}_{\text{RUTF}} \neq \text{rate}_{\text{Control}}$$

where  $\text{rate}_{\text{RUTF}}$  = rate of “negative nutritional outcome” in the children in the RUTF group, and  $\text{rate}_{\text{Control}}$  = rate of “negative nutritional outcome” in the children in the control group.

The comparison of rates among the two treatment groups (RUTF vs. control) will be performed by a Poisson regression model, adjusted for nutritional status at enrolment (fixed effect) and will be performed within one model including the three intervention groups with contrasts for each two-group comparison. The result will be presented as rates for each intervention group, and a rate ratio for the pair-wise comparison (each with 95% confidence intervals). Tests will be two-sided with a significance level of 0.05.

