#### 5.4.3 Subgroups

Stratified analysis will be done for three pair-wise comparisons (RUTF vs. control, MNP vs. control, RUTF vs. MNP (as described in 5.4.1) according to the following subgroups (measured at baseline):

- age (binary: <36 months, ≥36 months)
- gender
- current breastfeeding practices (no, partial breast feeding)
- underlying illnesses (only malaria, only diarrhoea, only LRTI, 2 or more diseases)
- socio-economic status (low, moderate, high)
- food availability (binary or in tertile)
- length of illness before visiting MSF clinic (binary or in tertile)
- recruitment period (binary or in tertile)
- malnourishment status(non-acutely malnourished or moderately acutely malnourished)

To assess the presence of effect modification for these factors, models with interaction terms will be analysed.

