## **5.5 Analysis of secondary endpoints**

All secondary endpoints (as defined in section 3.2) will be compared between the three treatment groups as described in 5.4.1 (p-values will be considered explorative) for the ITT and the PP populations. In addition to the Poisson regression model, logistic regression model, analysis of variance (ANOVA), analysis of covariance (ANCOVA), Cox proportional hazard model, and non-parametric analysis of variance will be used, according to the type of endpoint. In case of relevant differences in baseline characteristics additional adjustment(s) for these factors may be performed. Stratified analyses are planned for secondary endpoints regarding weight and weight change with respect to age, gender, and breast feeding.

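### SAP 5.4.2 and 5.5 choose extra covariates because arms differ at baseline rather than because they predict the outcome, and the fixed primary model adjusts only for nutritional status, so some power may be lost

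*SAP*

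**What the plan says.** **Primary model (SAP 5.3).** The RUTF-control comparison uses a "Poisson regression model, adjusted for nutritional status at enrolment (fixed effect"). This covariate is fixed in advance, and the closing paragraph of 5.4.1 carries the same model into all three hierarchical steps.

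**Levels of that covariate.** Section 5.3 does not state them. Two levels are inferred from the subgroup list in 5.4.3, "malnourishment status(non-acutely malnourished or moderately acutely malnourished"), and from the separate event definitions in 3.1. There, "for children with moderate malnourishment at time of entry into study, “negative nutritional outcome” is defined as loss of" at least a tenth of baseline weight or reaching severe malnourishment. Children not malnourished at entry have the event when they reach moderate or severe malnourishment.

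**Rule for further covariates.** Section 5.1 says: "Differences regarding baseline variables will be checked for clinical relevance between the three treatment groups". Section 5.4.2 follows with "In case of relevant differences in baseline characteristics additional adjustment(s) for these factors will be performed within the model described in 5.4.1", the stated purpose being "to address potential confounding". For secondary endpoints, 5.5 says: "In case of relevant differences in baseline characteristics additional adjustment(s) for these factors may be performed".

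**Not stated for this rule.** There is no candidate list, threshold or functional form, and no word on whether the choice is made blinded. By contrast, 5.4.4 gives the check of missing endpoint data to someone blinded to allocation and labels any imputation a sensitivity analysis.

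**The concern.** Under randomisation, baseline differences between arms arise by chance. What makes a covariate worth including is that it predicts the outcome, and the rule never asks this. It can bring in a factor that differs between arms but is irrelevant to malnutrition, and leave out a balanced one that is strongly prognostic.

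Three things are at stake.

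- **Discretion.** With no list or threshold, the covariates of the adjusted analysis depend on a judgement made after the group tables exist.
- **Status.** Section 5.4.2 adds covariates within the model of 5.4.1, which carries the hierarchical tests. It does not say which version decides a step if the two disagree.
- **Power.** A child's starting distance from the malnutrition threshold plausibly predicts who crosses it. A two-level status treats a child just above the threshold like one far above it. Baseline weight and the eight other baseline factors in 5.4.3 are recorded, but none is a fixed covariate.

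**Working it through.** The SAP states no sample size, event rate, effect size or power, so there is no figure of its own to reproduce. All inputs below are assumptions except the significance level (0.05, two-sided, from 5.3), the model form (5.3) and the count of eight baseline factors besides malnourishment status (5.4.3).

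**1. How often would a trigger fire by chance?** Suppose each of eight independent factors were flagged at p < 0.05. The SAP uses clinical relevance instead, so this is only an illustration. Then P(at least one flagged) = 1 − 0.95^8 = 1 − 0.663 = 0.337, or about a third of properly randomised trials.

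**2. Simulation of power.**

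- *Trial:* three arms of 500; first-event Poisson model with each child's time up to the event or end of follow-up as person-time; 20% moderately malnourished.
- *Rates:* baseline control rate 0.15 or 0.40 per follow-up period; true RUTF-control rate ratio 0.7.
- *Covariates:* one continuous baseline covariate with log-rate effect 0, 0.5 or 1.0 per SD, and eight binary factors with log-rate effect 0.2 each.
- *Runs:* 1500 per scenario.

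The triggered analysis adds any of the nine factors for which RUTF and control differ at |z| > 1.96. The trigger fired in 37% to 41% of simulated trials.

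| Control rate | Covariate effect per SD | Power, nutritional status only | Power, continuous covariate fixed in advance | Power, triggered |
|---|---|---|---|---|
| 0.15 | 0 | 55.8% | 55.9% | 55.7% |
| 0.15 | 0.5 | 54.1% | 56.3% | 54.6% |
| 0.15 | 1.0 | 55.3% | 68.3% | 56.4% |
| 0.40 | 0 | 88.7% | 88.5% | 88.6% |
| 0.40 | 0.5 | 86.2% | 89.6% | 87.1% |
| 0.40 | 1.0 | 80.7% | 92.3% | 82.0% |

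- Gain from fixing the covariate in advance: 0.1, 2.2 and 13.0 points at rate 0.15; −0.2, 3.4 and 11.6 points at rate 0.40.
- Gain from the trigger with the strong covariate: 56.4 − 55.3 = 1.1 points and 82.0 − 80.7 = 1.3 points.
- The Monte Carlo standard error of one power figure near 55% is √(0.55 × 0.45 / 1500) = 1.3 points. All models were fitted to the same simulated trials.

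**3. Where the gain comes from.** The mean standard error of the log rate ratio is the same with and without the covariate: 0.166 and 0.110 at effect 0.5 per SD, 0.149 and 0.105 at 1.0 (control rates 0.15 and 0.40). The estimate moves instead. At rate 0.40 and effect 1.0 the mean log rate ratio is −0.297 without the covariate and −0.356 with it; the true value is ln 0.7 = −0.357. The normal approximation agrees with the table:

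- without: 0.297 / 0.105 = 2.83, and Φ(2.83 − 1.96) = Φ(0.87) = 0.81;
- with: 0.356 / 0.105 = 3.39, and Φ(3.39 − 1.96) = Φ(1.43) = 0.92.

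Omitting a strong covariate pulls the first-event rate ratio towards 1. The adjusted ratio is conditional on that covariate.

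**4. Type I error (rate ratio 1.0).** Over the six null scenarios the rejection rate was 4.3% to 5.9% with nutritional status only, 4.6% to 5.9% with the fixed covariate and 4.3% to 5.6% when triggered. Claiming success if either the primary or the triggered model was significant gave 4.5% to 6.3%. The largest excess over the primary model in the same scenario was 4.9 − 4.4 = 0.5 points. Over all twelve scenarios, the primary and triggered models disagreed on significance in 0.5% to 2.9% of trials.

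**The case against.** The strongest reply is that no confirmatory result depends on the trigger. The primary covariate is fixed in 5.3, and 5.4.1 says the hierarchical steps use that same model. Section 5.4.2 sits under secondary analysis, and 5.5 calls its p-values exploratory. This largely stands: a reader might infer that the covariates of the primary analysis are chosen after seeing the data, and the text does not support that. What remains is that 5.4.2, unlike 5.4.4, does not label its result a sensitivity analysis.

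A reader might also infer that the choice is made on unblinded tables. Section 5.1 speaks only of a comparison between the three groups, so the fair statement is that blinding is not stated. The selection uses baseline data, not outcomes.

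Two further stronger readings fail on the numbers. One is that the error rate of the adjusted analysis becomes unreliable; type I error stayed close to nominal. The other is that precision is lost; the standard error hardly moves, and what can be lost is power.

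The power argument can be challenged too. The larger gains need an effect of 1.0 log-rate per SD, a 2.7-fold change in rate (e^1.0 = 2.72). At 0.5 per SD the gain is 2 to 3 points, and with no effect it is nil. The SAP does not show that age or presenting illness is prognostic, and it names no continuous anthropometric measure. This stands as a limit on the size of the point.

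Finally, the two-level status is not an arbitrary split: it encodes which event definition in 3.1 applies to the child. This stands, so it must stay in the model, and a single continuous slope across both groups could be misspecified. Section 5.5 already lists ANCOVA, but does not assign it to an endpoint or name its covariates.

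**Conclusion.** The concern holds in this limited form. The trigger in 5.4.2 and 5.5 is a poor way to choose covariates, whatever its effect on error rates. It selects on chance imbalance, leaves room for discretion, and leaves unclear how the further-adjusted result stands to the hierarchical steps.

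The primary model is valid and pre-specified. It may give up power by adjusting only for nutritional status: about 0 to 13 points, depending almost wholly on how prognostic the omitted covariate is. Triggered adjustment recovered only about 1 point with a strong covariate.

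These figures rest on the assumed inputs listed above, on person-time that ends at the first event, and on the two-level reading of nutritional status. They show a plausible range, not an estimate for this trial. The change is worth making because it costs little.

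**What to change.** Before unblinding, amend the SAP as follows.

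- Delete the two sentences in 5.4.2 and 5.5 that make adjustment depend on observed baseline differences.
- Name a short, fixed list of prognostic baseline covariates, with functional form, to be added to the Poisson model alongside nutritional status. Examples are age in months, presenting illness in the four groups of 5.4.3 and, if the protocol records one, the continuous baseline anthropometric measure, with its slope allowed to differ by nutritional status.
- For the weight endpoints, specify ANCOVA with baseline weight and age.
- Report the model with nutritional status alone as a sensitivity analysis.
- State that a model with any other covariates is a sensitivity analysis and does not govern the hierarchical procedure.

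The cost is SAP wording, a few more parameters and a simple rule for missing baseline values. The descriptive baseline comparison in 5.1 can stay, provided that it no longer drives the choice of model.
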